### Participant Identification

#### Screening

Individuals attending the outpatient department of NARIP identified as likely eligible to participate in the study will be given a participant information sheet. A trial team member will check initial eligibility if interested in participating. If the person is likely eligible, the researcher will send them to ICCONS for further screening.

#### Eligibility Confirmation

Eligibility confirmation will be done at ICCONS by an experienced audiologist and neurologist. This assessment will include tympanometry, PTA, and Montreal Cognitive Assessment (MoCA). Only patients with a pure tone average of 26-55 dB hearing loss will be included.

#### Consent

Written informed consent would be obtained before starting trial-related procedures or data collection. A suitably qualified and experienced person delegated by the principal investigator will get the consent. We have pilot tested the readability and comprehension level of the consent materials. For participants with literacy challenges and visual impairment, the bystander of the participant will help in the informed consent process.

### Interventions

#### Comparator

In BTHE, participants will receive treatment for diabetes mellitus, hypertension, and dyslipidemia and counsel related to lifestyle modification and avoiding alcohol and cigarette use. Advice on optimizing individual acoustic environments is provided, including reducing background noise and engaging in face-to-face conversations to maximize exposure to nonverbal communication cues. Lip reading classes will also be offered. This ancillary care is provided within the scope of this trial.

#### TOPMAC Intervention

The topical oil pooling will be done on weeks 1, 5, 9, 13, 17, and 21. The preparatory procedure includes temporal region massage with processed gingelly oil (Murchita Tila Taila) followed by sudation therapy. The main therapeutic procedure is to instill 5 mL of Kshirabala Taila in each auditory canal for 15-20 minutes in the morning. The therapy procedure includes massaging the ear base, and after 15-20 minutes, the oil will be wiped with dry cotton. Ashwagandha Churna will be supplemented with a dose of 6 grams at bedtime with 10 mL of cow’s ghee for 24 weeks. Participants in both groups are covered under clinical trial insurance.

### Study Training

A trained Panchakarma therapist will perform the topical oil pooling per the institute’s standard operating procedure (SOP). Trained technicians from ICCONS would perform all the audiometry evaluations. The investigator’s brochure and SOPs developed for the project are communicated to all the investigators. Further intermittent meetings of the investigators are planned. The reorientation/interaction with the study staff is repeated periodically during the investigators’ meeting.

### Concurrent Health Care for All Participants

All participants would be instructed to access routine health care, including medicines and consultations, with other health professionals. The details of the cointerventions would be noted at the assessments on day 29, day 57, day 85, day 113, and day 141.

### Primary Outcomes

The primary outcomes include differences in the average 500 Hz, 1 kHz, and 2 kHz in PTA from baseline and after the 24th week of intervention. PTA is the gold standard for measuring sensitivity and identifying the presence and degree of hearing loss. PTA (isolated frequency) over a range of frequencies critical for everyday listening can determine the degree, configuration, and type of hearing loss in a manner detailed enough to assist the health care team in determining the etiology and prognosis for the hearing loss as well as the optimal treatment strategy [24]. Pure-tone evaluation is typically performed in a sound-treated booth to reduce the impact of external sounds, with the booth environment and electroacoustic equipment calibrated to American National Standards Institute standards to optimize intertest and intratest reliability. Primary outcomes also include Brainstem Evoked Response Audiometry (BERA) changes and differences in speech recognition threshold and speech discrimination score.

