## Introduction

Presbycusis (age-related hearing loss) is characterized by sensorineural hearing loss at high frequencies in both ears, delayed central processing of auditory information, and problems understanding speech in loud environments [1]. It is usually associated with an audiogram that reveals the greatest hearing loss at higher frequencies. It affects over half of the older adults by the age of 75 years and nearly all older than 90 years [2]. Hearing loss is often accompanied by tinnitus. Many extensive population-based longitudinal studies have recommended that presbycusis is independently connected with cognitive deterioration.

The issues and effects of presbycusis are exacerbated in older adults due to additional degenerative processes in the central nervous system, which can lead to loss of neuroplasticity, cognitive ability, and other sensory modes, particularly vision [3]. Age-related hearing loss has an impact on both psychological well-being and physical ability. Some recent studies have established independent associations of hearing loss with driving ability, walking difficulty, social isolation, functional decline, and falls [4]. Social isolation causes emotions of incarceration and anxiety, which reduce higher cognitive performance, potentially increasing the economic and societal burden of age-related hearing loss [5]. The risk factors include age, male sex, diabetes mellitus, hypertension, and hereditary hearing loss [6]. Diabetes or hypertension, if not appropriately controlled, may also cause hearing problems through chronic arteriosclerosis. These are common chronic diseases in the aged population, leading to reduced blood flow in the inner ear [6]. Presbycusis is a serious but primarily neglected condition in India. The Indian government has started the National Program for Prevention and Control of Deafness to benefit the deaf population. The aims of this program include medically rehabilitating deaf persons of all age groups and fortifying the existing intersectoral linkages to maintain the rehabilitation program [7].

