### Eligibility Criteria

The intended population is adults aged 60-75 years diagnosed with mild to moderate presbycusis. Pure tone audiometry (PTA) will be performed for octave frequencies between 0.25 and 8 kHz, and the pure tone average will be calculated for 500 Hz, 1 kHz, and 2 kHz. The patients with a pure tone average of 26-55 dB hearing loss will be included. The other eligibility criteria are shown in Textbox 1.

Eligibility criteria.

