### Sample Size Determination

A previously published report on the administration of topical oil pooling in patients with presbycusis showed that the average hearing level for the frequency of 500 Hz, 1 kHz, and 2 kHz after treatment was 53 dB (for air conduction defect of the right and left ears) [11]. We based our sample size calculation on the assumption that the average hearing level at these 3 frequencies will be 50 dB in the TOPMAC+BTHE group, while it will be 60 dB in the BTHE group. A difference of 10 dB after treatment between both groups has been considered clinically meaningful. With a standard deviation of 12 dB, 80% power, and a confidence interval of 95%, the calculated sample size for each arm is 23. The sample size becomes 28.75, rounded to 30 per arm, adding an attrition rate of 25%. Therefore, 60 participants must be enrolled in the trial (30 in each arm). The attrition rate was based on the clinical experience in treatment compliance. Moreover, in a previous study [25] on Ayurveda interventions among older participants, such attrition had occurred. An interim analysis will be performed after 25% of the participants complete the study duration, and then the reassessment of the attrition rate will be considered along with the original sample size.

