### Conclusion

If this exploratory trial is proven effective, it will steer the setting of a definitive randomized controlled trial, which will incorporate the limitations as described above, to test whether the TOPMAC intervention can be incorporated as a cost-effective integrative approach for managing presbycusis.

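### Four hearing measures are named as primary without a ranking or success rule, although the trial is sized on only one of them

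*Protocol article*

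**What the plan says.** The Primary Outcomes section of the protocol article begins with audiometry: "The primary outcomes include differences in the average 500 Hz, 1 kHz, and 2 kHz in PTA from baseline and after the 24th week of" … It closes with three further measures at the same level: "Primary outcomes also include Brainstem Evoked Response Audiometry (BERA) changes and differences in speech recognition threshold and speech discrimination score". Nothing in that section, or in Statistical Methods, calls one of the four the main outcome or says how they combine.

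Sample Size Determination uses only the first. Its assumption for the two arms reads: "the average hearing level at these 3 frequencies will be 50 dB in the TOPMAC+BTHE group, while it will be 60 dB in the BTHE" … It adds: "A difference of 10 dB after treatment between both groups has been considered clinically meaningful". The result is: "With a standard deviation of 12 dB, 80% power, and a confidence interval of 95%, the calculated sample size for each arm is 23". No effect or standard deviation is given for brainstem evoked response audiometry (BERA), speech recognition threshold or speech discrimination score.

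The Conclusion gives the result a consequence: "If this exploratory trial is proven effective, it will steer the setting of a definitive randomized controlled trial". The Conclusions paragraph of the Abstract says the same. Neither says which outcome decides.

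**The concern.** With four unranked primary outcomes and no rule, two opposite readings of success are open. Under one, a positive result on any of the four is enough, and the false-positive risk for the trial as a whole exceeds 5%. Under the other, all four must be positive, and the power falls short of the 80% planned for one. The choice between them would be made after the results are known, by a statistician who, according to the section on randomization and blinding, is not blinded to allocation. What is at stake is the decision to start a definitive trial.

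**Working it through.** **Inputs from Sample Size Determination.** Difference 10 dB, SD 12 dB, power 80%, 95% confidence (read as two-sided alpha 0.05), 23 per arm before attrition. **From Primary Outcomes.** Four measures. **Assumed, not in the document.** Correlations between the four test statistics, and 80% power for each of the three measures that were not sized.

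**1. The plan's own figure.** n per arm = 2 × [SD × (z₀.₉₇₅ + z₀.₈₀) / difference]² = 2 × [12 × (1.960 + 0.842) / 10]² = 22.6, rounded up to 23. The stated figure is reproduced. It is the size for one outcome tested at 5%.

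**2. If any one of four counts as success.** With no true effect and independent tests, the chance of at least one p < 0.05 is 1 − 0.95⁴ = 0.185. Hearing measures on the same person are likely to be correlated, which lowers this. For four equally correlated normal test statistics:

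| Assumed correlation | Chance of at least one false positive |
|---|---|
| 0 | 18.5% |
| 0.3 | 17.4% |
| 0.5 | 15.6% |
| 0.7 | 13.0% |
| 0.9 | 9.4% |

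**3. If all four must succeed.** The false-positive risk is then at most 5%, but power suffers. With 80% power for each, joint power is 0.8⁴ = 41% if independent, and 50%, 56%, 62% and 70% at correlations of 0.3, 0.5, 0.7 and 0.9. Joint power can never exceed that of the weakest of the four.

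**4. If the four shared a 5% error rate equally (illustration only).** Alpha per test is 0.05 / 4 = 0.0125, with critical value 2.498. Then n = 2 × [12 × (2.498 + 0.842) / 10]² = 32.1, rounded up to 33 evaluable per arm, against 23. At 23 per arm, power for the 10 dB difference would be 63%.

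**5. One primary outcome.** Naming the pure tone average alone leaves step 1 unchanged: 23 per arm, 23 × 1.25 = 28.75 with the plan's attrition allowance, rounded in the plan to 30.

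The stated sample size therefore matches its error rate and power only under the single-primary reading.

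**The case against.** The trial is called exploratory throughout, and a false lead would be tested again in the definitive trial. That stands, and it lowers the need for formal error control; it is the reason for proposing one named outcome rather than a split of alpha. It does not remove the need to say which result triggers the next trial.

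A method for multiple outcomes may sit in a full protocol or analysis plan that is not shown. That also stands, so the absence of an adjustment method is not the point. The designation of four equal primary outcomes is made in this document.

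The pure tone average has priority in practice: it comes first, is described as the reference standard, decides eligibility and sets the sample size. This is fair, and it makes the fix a natural one. It is still not a stated ranking.

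Three stronger readings are tempting, and the document does not support them:

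- A reader might infer that the trial has an 18.5% false-positive rate. That needs a rule by which any one result suffices, and none is stated.
- A reader might count several BERA measures or both ears and go higher, for example 1 − 0.95⁸ = 34% for eight independent tests. The document gives no such count, and two ears of one person are not independent.
- A reader might call it an error that the average stops at 2 kHz, since the Introduction says of the condition: "It is usually associated with an audiogram that reveals the greatest hearing loss at higher frequencies". The three-frequency average agrees with the eligibility measure and with the sample size, so the choice is consistent and is not a mistake.

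**Conclusion.** The point holds in this form: the protocol names four primary hearing outcomes, sizes the trial on one, and attaches a go decision to effectiveness without saying which outcome settles it. The size depends on the rule eventually applied. Under an any-one rule the false-positive risk is between about 9% (correlation 0.9) and 18.5% (independence). Under an all-four rule with 80% power for each, joint power is about 41% to 70% over the same range. The rules, the correlations and the power of the three unsized outcomes are assumptions. The list of four, the single sized outcome and the missing success rule are on the page. The sample size arithmetic itself is not in question. This should be corrected, but in a trial labelled exploratory it does not invalidate the design.

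**What to change.** In Primary Outcomes, name the between-arm difference in the 0.5, 1 and 2 kHz pure tone average at Day 169 as the single primary outcome. In the Conclusion and the Abstract, tie the finding of effectiveness to that outcome alone. Move BERA, speech recognition threshold and speech discrimination score to Secondary Outcomes, reported as estimates with 95% confidence intervals.

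Optionally, add the 4 and 8 kHz average as a named secondary outcome. Eligibility Criteria states: "Pure tone audiometry (PTA) will be performed for octave frequencies between 0.25 and 8 kHz". For follow-up, however, Table 1 lists only the pure tone average and the text only PTA, so first confirm that the full audiogram is repeated at Day 169.

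The cost is wording in the protocol and the registry entry, with no new visits or participants. Two things are given up or required. A BERA or speech result alone can no longer be called a primary success. And the change comes late: 22 participants were enrolled by August 2024, participants, treating investigators and statistician are unblinded (the audiometric assessor is blinded), and an interim analysis is planned once 25% (0.25 × 60 = 15) have completed. The Results section says analysis had not started. The amendment should be dated and should record that no between-arm data had been seen.

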### Secondary Outcomes

The secondary outcomes consist of differences in the tinnitus functional index (TFI) from baseline and after the 24th week of intervention. The secondary outcome also includes the MoCA score difference. TFI is considered the gold standard for measuring tinnitus severity. It is a 25-item questionnaire that identifies the tinnitus severity of the patient by calculating the overall TFI score. The 8 subscales address 8 critical domains of negative tinnitus impact: I, intrusive (unpleasantness, intrusiveness, persistence); SC, sense of control (reduced sense of control); C, cognitive (cognitive interference); SL, sleep (sleep disturbance); A, auditory (auditory difficulties attributed to tinnitus); R, relaxation (interference with relaxation); Q, quality of life (quality of life reduced); and E, emotional (emotional distress). In this way, the TFI score and subscore will measure the improvement in subjective well-being and quality of life related to tinnitus.

### Adverse Events

Any adverse event or adverse drug reaction, if seen during the trial period, will be documented suitably, and timely management would be performed, and the same would be reported to the ethics committee and the sponsor(s) at the earliest. Considering the participant’s age and the character of the intervention, predictable adverse events include gastrointestinal side effects (nausea, vomiting, and diarrhea), dizziness, fatigue, ear pain, itching in the ears, and fullness in the ears. Safety reporting would begin from the point of randomization and finish when the participant has finished their 169th-day assessment.

### Sample Size Determination

A previously published report on the administration of topical oil pooling in patients with presbycusis showed that the average hearing level for the frequency of 500 Hz, 1 kHz, and 2 kHz after treatment was 53 dB (for air conduction defect of the right and left ears) [11]. We based our sample size calculation on the assumption that the average hearing level at these 3 frequencies will be 50 dB in the TOPMAC+BTHE group, while it will be 60 dB in the BTHE group. A difference of 10 dB after treatment between both groups has been considered clinically meaningful. With a standard deviation of 12 dB, 80% power, and a confidence interval of 95%, the calculated sample size for each arm is 23. The sample size becomes 28.75, rounded to 30 per arm, adding an attrition rate of 25%. Therefore, 60 participants must be enrolled in the trial (30 in each arm). The attrition rate was based on the clinical experience in treatment compliance. Moreover, in a previous study [25] on Ayurveda interventions among older participants, such attrition had occurred. An interim analysis will be performed after 25% of the participants complete the study duration, and then the reassessment of the attrition rate will be considered along with the original sample size.

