## Methods

### Trial Design

This is a multicenter, parallel, 2-group, exploratory, randomized (1:1) controlled trial. The plan of enrollment, interventions, and assessments is given in Table 1.

**Table 1 table1:** Schedule of enrollment, interventions, and assessments for the TOPMAC (Topical Oil Pooling with Kshirabala Taila and Supplementation of Ashwagandha Churna) study.

			Screening		Baseline		Intervention period											End of treatment
Timepoint					Day 1		Day 29		Day 57		Day 85		Day 113		Day 141		Day 169	
	Potential participant identification and screening	✓																
	Provision of participant information sheet	✓																
	Eligibility assessment	✓																
	Informed consent	✓																

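### The 25% attrition allowance is computed as 23 × 1.25 = 28.75 instead of 23/0.75 = 30.67; rounding up to 30 per arm absorbs most of the slip, so the effect on power is minor

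*Protocol article*

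**What the plan says.** All of the relevant text is in the protocol article under Sample Size Determination. The assumed post-treatment hearing levels "will be 50 dB in the TOPMAC+BTHE group, while it will be 60 dB in the BTHE group", and the gap is justified as follows: "A difference of 10 dB after treatment between both groups has been considered clinically meaningful". The evaluable number is then given: "With a standard deviation of 12 dB, 80% power, and a confidence interval of 95%, the calculated sample size for each arm is 23". The allowance for loss follows: "The sample size becomes 28.75, rounded to 30 per arm, adding an attrition rate of 25" percent. Total enrolment is set at 60, or 30 per arm, which agrees with the 1:1 allocation under Trial Design. The 25% rate is attributed to clinical experience with compliance and to an earlier study of Ayurveda interventions in older participants. An interim look is planned once a quarter of the participants have completed, at which "the reassessment of the attrition rate will be considered along with the original sample size".

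**The concern.** An attrition rate is a share of those enrolled, so the number enrolled, multiplied by one minus the rate, must equal the number needed for analysis. Adding 25% to the evaluable number does something else. Losing 25% of 28.75 leaves 21.56, not 23. The text therefore presents as a 25% attrition allowance a figure that does not provide one.

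Two things are at stake. The first is whether 30 per arm delivers the stated power at the stated attrition. The second is whether the same shortcut might be used again when attrition is reassessed at the interim, where a higher observed rate would make the error larger.

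**Working it through.** **Inputs** (all from Sample Size Determination): difference 60 − 50 = 10 dB; SD 12 dB; power 80%; 95% confidence; attrition 25%. Two equal arms come from Trial Design. The confidence level is read as two-sided alpha of 0.05. The protocol does not state sidedness, but the two-sided reading reproduces its 23, whereas a one-sided reading gives 18.

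**Step 1. Reproduce the evaluable number.**
n = 2 × (1.96 + 0.8416)² × 12² / 10² = 22.60, rounded up to 23 per arm. This matches the protocol.

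**Step 2. Reproduce the allowance.**
23 × (1 + 0.25) = 28.75. This matches exactly and identifies the method used.

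**Step 3. Apply the allowance correctly.**
23 / (1 − 0.25) = 30.67, rounded up to 31 per arm, 62 in total. Expected completers are 31 × 0.75 = 23.25 per arm. The protocol's 30 is one per arm lower.

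**Step 4. What 30 per arm leaves.**
30 × 0.75 = 22.5 per arm, 45 in total. That is 0.5 per arm below 23 and 0.1 per arm below the unrounded requirement of 22.60. Had the protocol rounded 28.75 only to 29, it would have left 29 × 0.75 = 21.75.

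**Step 5. Power at those numbers.** The normal-approximation power is Φ(√(n/2) × 10/12 − 1.96). At n = 22.5 this is Φ(2.795 − 1.96) = Φ(0.835) = 79.8%. The t-test column is the power of a two-sided two-sample t test with the same inputs.

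| Completers per arm | Normal approximation | Two-sample t test |
|---|---|---|
| 22 | 78.9% | 77.0% |
| 22.5 (same for a 22/23 split) | 79.8% | 78.0% |
| 23 | 80.7% | 78.9% |
| 24 | 82.3% | 80.7% |

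Falling from 23 to 22.5 completers costs 0.9 percentage points in either column.

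**Step 6. Attrition that 30 per arm can bear.**
1 − 23/30 = 23.3%.

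**Step 7. How the shortcut behaves at other rates, starting from 23 completers.**

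| Attrition | 23 × (1 + rate) | 23 / (1 − rate) | Gap per arm |
|---|---|---|---|
| 25% | 28.75 | 30.67 | 1.9 |
| 30% | 29.9 | 32.9 | 3.0 |
| 40% | 32.2 | 38.3 | 6.1 |

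At 30% attrition the multiplier would indicate that 30 per arm is still enough, when 33 would be needed.

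**The case against.** The strongest reply is that the enrolled number is close to right whatever the route to it. The protocol enrols 30, not 28.75 or 29, and the correct figure is 31. The unrounded requirement is 22.60, and 30 per arm is expected to leave 22.5. The 25% is itself an estimate, and the distance between 23.3% and 25% lies well within its uncertainty. The trial is described as exploratory, and Data Management foresees imputation of missing values, so an analysis of completers only is not fixed. All of this stands, although imputation does not fully restore lost information. It limits the size of the point but does not make the 28.75 step correct.

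A reader might infer three stronger things, and the document does not support them.

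- *That the attrition slip costs 2 to 3 points of power.* Most of such a loss comes from replacing the normal approximation with a t-test calculation, under which 23 completers already give 78.9%. The slip adds 0.9 points. A figure of 77.0% needs 22 completers in both arms, which is 1 − 44/60 = 26.7% attrition rather than 25%.
- *That the evaluable number should be 24, hence 32 per arm, because the plan uses a t test.* The t-test requirement is indeed 23.6, rounded up to 24. But Statistical Methods names the t test only for parametric values, next to the Mann-Whitney test and regression adjustment, and planning by the normal approximation is common practice. The 23 is not an error.
- *That the interim reassessment will repeat the mistake.* The protocol gives no formula for that step. Reuse of the multiplier is a risk, not something the plan states.

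**Conclusion.** The attrition step is wrong as written: 28.75 can only be 23 × 1.25, and 25% attrition calls for 30.67, or 31 per arm. The effect is minor. At the protocol's own attrition rate, 30 per arm gives an expected 22.5 completers per arm, with power of 79.8% by the formula behind its 23 and 78.0% by a t-test calculation. The document does not support a claim that the trial is materially underpowered for this reason, nor that more participants must be enrolled.

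These figures rest on the protocol's 10 dB difference and 12 dB SD, two-sided alpha of 0.05, loss spread evenly over the two arms, and an analysis of those who complete.

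**What to change.** Keep 30 per arm and 60 in total. In Sample Size Determination, replace the 28.75 step with n/(1 − attrition) and then state one of the following:

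- that 30 per arm preserves 23 completers up to about 23% attrition; or
- that with 25% attrition about 22.5 per arm (45 in total) are expected to complete, with power just under 80% by the normal approximation and about 78% by a two-sample t test.

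State also that the interim reassessment will use n/(1 − attrition) with the observed rate. At 25% the rounding to 30 hides most of the error, but at a higher rate it would not.

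The cost is one or two sentences. No participants are added, and the design and analysis do not change.
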